### Sample size

The sample size for the primary outcome (HR-QoL) was estimated by using the formula to test change in the mean of two normally distributed samples in longitudinal studies [50]. An average increase of at least 10 points in one or more domains of WHQ23 in the intervention group compared with control group women was considered to be clinically relevant. The assumptions included: a mean HR-QoL score of 64.9 points (standard deviation of 23.4 points) in the domain of general well-being [51], α = 0.05 (for one-sided hypothesis) and β = 0.20. The number of women by group, assuming a drop-out rate of 20% will be 107.

We also estimated a sample size for regular leisure time physical activity considering that this is the outcome variable more difficult to achieve. It was assumed that only 17% of women in Mexico engaged in some type of regular leisure time physical activity [11] and a positive increase of at least 10% will be achieved after women participation in the IHCM. For this calculation, we used the formula to test the difference of proportions between two populations [50] with a = 0.05 (one side) and the power of 80%. The total number of women by group to include assuming a drop-out rate of 20% will be 207.

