### Data collection

Information on the study variables will be collected on three occasions: when the woman enters to the study (baseline), once intervention is complete (at three months) and after three more months of follow-up (six months).

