### Study variables

The main outcome variables will be:

Health-related quality of life (HR-QoL), which will be measured with the revised version of Women's Health Questionnaire (WHQ23) [43]. This is a specific questionnaire for women in perimenopause, menopause and post menopause stages, that comprises six domains: anxiety/depression, well-being, somatic symptoms, memory/concentration, vasomotor symptoms and sleep problems. The WHQ23 also has two optional domains: sexual behavior and menstrual symptoms, which will apply only to women who are sexually active or who have menstrual periods. The highest value for each domain score is 100, which means high HR-QoL, and the lowest is 0, which means low HR-QoL.

Other outcome variables will be:

1) Empowerment of women in relation to their self-care measured by the empowerment scale, which was modified from the diabetes empowerment short scale [44] to be used in climacteric women. The maximum score of empowerment is 5, the minimum is 1.

2) Self-efficacy of women in relation to menopause and its care will be assessed with Perimenopausal Health Self-efficacy Scale (PHS-ES) which consists of 23 items [45]. The maximum score of PHS-ES is 207 (high self-efficacy) and the minimum is 23 (low self-efficacy).

3) Women's knowledge about the climacteric stage will be estimated with a questionnaire developed *ex profeso*. The questionnaire consists of 24 items that assess the following aspects: what is the climacteric stage, what are climacteric symptoms and health risks, and how can they be prevented during the climacteric stage. The minimum score on the scale corresponds to -24 points (without knowledge) and the maximum 24 points (full knowledge).

4) The use of screening services for: a) breast cancer by mammography in the last two years; b) cervical cancer by Pap-test in the last three years in women without a history of total hysterectomy; c) diabetes by measuring fasting plasma glucose in the last three years; d) hypertension: by measuring the systolic and diastolic blood pressure in the last year. The use of screening services will be estimated as the sum of the number of screening services that women used, divided by the total number of screening services recommended according to IMSS regulations and multiplied by 100.

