### Statistical analysis

The women characteristics of each intervention and comparison groups will be compared by using the Chi-square test to ascertain whether the groups were equivalent.

The effects of intervention for categorical outcome variables (regular leisure time physical activity, healthy diet) will be measured by comparing the baseline and post-intervention evaluation stages for differences in these variables using Chi-square test. Absolute percentage differences and corresponding 95% confidence intervals will be calculated.

Scores for the HR-QoL on the WHQ23 scale, the self-efficacy on the PHS-ES scale, the empowerment on the short form scale, knowledge about the climacteric stage, and menopause and self-care-related activities will be calculated according to the scoring algorithms. Measures of central tendency and distribution will be examined for these variables at the different measurement periods. The differences in the baseline and post-intervention stages for outcome variables will be compared within each group, and differences between the groups will be compared using the differences-in-differences (D-in-D) estimator [52]. The generalized linear model (GLM) will be used to assess changes in the main outcome variable controlling for baseline measures and other study variables as covariates. The GLM methods allow for modeling the correlation of the repeated observations on the same subjects [53].

The p value <0.05 will be considered as statistically significant. The analysis will be performed with the Stata 11.0 statistical software (Stata 11.0, Stata Corp; College Station, TX).

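### The relevant effect on the primary outcome may fall in any WHQ23 domain, but alpha and sample size are set for one domain only

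*Protocol article*

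**What the plan says.** All references are to the Methods/Design part of the protocol article.

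- **Study variables.** The main outcome is health-related quality of life, measured with a questionnaire "that comprises six domains: anxiety/depression, well-being, somatic symptoms, memory/concentration, vasomotor symptoms and sleep problems". There are also "two optional domains: sexual behavior and menstrual symptoms, which will apply only to women who are sexually active or who have menstrual periods". Each domain has its own 0 to 100 score ("The highest value for each domain score is 100, which means high HR-QoL"). No total score is described and no domain is named as primary.
- **Sample size.** The effect regarded as clinically relevant, against control, is "An average increase of at least 10 points in one or more domains of WHQ23 in the intervention group". The calculation then uses a mean of 64.9 and an SD of 23.4 from general well-being alone, alpha 0.05 one-sided, beta 0.20 and 20% drop-out, and arrives at 107 women per group. A second calculation, for physical activity, arrives at 207 per group.
- **Data collection.** After baseline, measurements are taken "once intervention is complete (at three months) and after three more months of follow-up (six months"). Neither visit is named as primary.
- **Statistical analysis.** Changes are compared between groups by difference-in-differences and a generalized linear model. The only criterion is "The p value <0.05 will be considered as statistically significant". It does not mention domains, sidedness or adjustment.

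**The concern.** An effect that may appear in any of several domains is a statement about a family of comparisons. An alpha of 0.05 and a sample size built on one domain's SD describe a single comparison. The two stand together in the Sample size section but do not belong to the same test.

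At stake is the main conclusion on effectiveness. If one domain turns out significant, a reader cannot tell from this text whether it was the intended test or the best of six, so the error rate behind the claim is not fixed. This goes beyond detail that an article may leave to a fuller document: an adjustment could be specified elsewhere, but the 107 per group makes no allowance for one.

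**Working it through.** **Inputs from the article:** difference 10, SD 23.4, alpha 0.05, power 80%, drop-out 20%, six core domains, two optional domains, two post-baseline visits, 107 and 207 per group. **Assumption:** a common correlation ρ between domain test statistics. The article gives none, so a range is shown.

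**1. The plan's own figure.** n = 2 × [23.4 × (z_α + z_0.80) / 10]².
- Two-sided 0.05: 85.95 per group; 85.95 / 0.80 = 107.4, which matches 107.
- One-sided 0.05, as the text states: 67.7, rounded up to 68; 68 / 0.80 = 85, which does not match.
- A one-sided calculation on change scores comes close (86 completers, 108 enrolled) if the baseline to follow-up correlation is about 0.37, a value the article does not give.

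On any of these routes, 107 is the size for one comparison at unadjusted 0.05.

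**2. Error if any domain at one-sided 0.05 supports the claim.**
- Independent domains: 1 − 0.95⁶ = 0.265; 1 − 0.95⁸ = 0.337.
- Correlated domains: 1 − ∫ Φ[(1.645 − √ρ·u) / √(1 − ρ)]^k φ(u) du.

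| Assumed ρ | 6 core domains | 8 domains |
|---|---|---|
| 0 | 26.5% | 33.7% |
| 0.3 | 22.0% | 26.7% |
| 0.5 | 18.6% | 21.9% |
| 0.7 | 14.8% | 16.8% |
| 0.9 | 10.0% | 10.9% |

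If the analysis threshold is two-sided and only benefit is claimed, six domains give 14.1% (ρ = 0), 10.4% (0.5) and 5.4% (0.9), against 2.5% for a single test.

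If both visits also counted, six core domains at one-sided 0.05 would give about 29%, assuming ρ = 0.5 between domains and 0.6 over time.

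**3. Error if an observed gain of at least 10 points were the requirement.**
- With 86 completers per group the standard error is 23.4 × √(2/86) = 3.57. The one-sided tail beyond 10 / 3.57 = 2.80 is 0.0025.
- For six independent domains: 1 − (1 − 0.0025)⁶ = 1.5%.
- This depends on the SD of the analysed change. With no baseline to follow-up correlation that SD is 23.4 × √2 = 33.1, and the same rule gives about 13%.

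**4. Power with adjustment across six domains.** 0.05/6 = 0.0083 two-sided, critical value 2.64.
- 86 completers: Φ(2.80 − 2.64) = 56.5%, down from 80.0% unadjusted.
- 207 enrolled: 207 × 0.80 = 165.6, about 166 completers. Standard error 23.4 × √(2/166) = 2.57; Φ(10/2.57 − 2.64) = Φ(3.89 − 2.64) = 89.5%.
- 80% power at this threshold needs 133 completers, and 133 / 0.80 = 166.25, so 167 enrolled per group.

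**The case against.** **The any-domain phrase is not a decision rule.** It defines the relevant effect for sizing. A reader might infer that the plan declares success when any domain reaches p<0.05. The article does not say so: its threshold is generic, and the analysis section speaks of the main outcome variable in the singular. This objection stands, so the error rates in step 2 are conditional. What remains is that the phrase is the article's only description of a relevant effect on this outcome, and nothing else narrows the primary test.

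**Read in full, the phrase also asks for 10 points.** If both 10 points and significance were required, the error could be as low as 1.5% (step 3). That is correct under its assumptions, but the article states no such joint rule.

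**The number of looks can be exaggerated.** Eight domains at two visits suggest 16 chances of success. The documents do not support that count. Two domains are optional and are given no role in the primary claim, and the planned model for repeated observations may handle both visits together. Equally, one cannot infer that the optional domains will be compared in different women over time, because their analysis is not described. The repeated-measures model does not, however, correct for several domains.

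**Inflation depends on correlation.** At 0.9 the one-sided error only doubles. This also stands.

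**A reader might infer from the 56.5% that adjustment is unaffordable.** It reflects only the smaller of the two sample sizes. At 207 per group, adjustment across six domains is affordable.

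**Adjustment may be specified elsewhere.** It may, and its absence from an article is not the complaint. The complaint is that the article's target effect and its alpha do not match.

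**Conclusion.** The point holds as a mismatch between the stated target (any domain) and the stated alpha and sample size (one domain, one test), with no primary domain or visit to settle it. If any core domain at one-sided 0.05 supports the claim, the false-positive chance is between 26.5% (independent) and about 10% (correlation 0.9), and about 19% at 0.5. So the nominal 5% does not hold on that reading. The optional domains and the second visit would add to this only if they also count towards the claim. The article neither adopts nor excludes that reading. The figures rest on assumed correlations, and those for power and the 10-point rule also rest on SD 23.4 applying to each domain.

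**What to change.** Replace the any-domain wording with one controlled primary test at one named time point (three or six months), in either of two ways.

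- **(a) One domain.** Make general well-being, the domain that was sized, the primary test, with the other five core domains and the other visit secondary. Planned power is unchanged. The cost is that a gain in another domain alone becomes a secondary result.
- **(b) Six domains.** Test all six core domains with Holm adjustment. With 207 per group (about 166 completers), power per domain at the strictest step, 0.05/6 two-sided, is about 89.5%, assuming SD 23.4 in each and ignoring clustering by clinic. The cost is a stricter threshold for each domain. The article should also state that 207, not 107, governs enrolment, because at 107 the power would be about 56.5%.

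The choice between them is scientific; both control the error. Under either, keep the two optional domains out of the primary claim, since they apply only to some women. State the sidedness of the test once and make the 107 agree with it (step 1 of the working). The change is to wording and needs no additional women beyond the larger sample size already given.

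### The physical-activity sample size of 207 per group does not deliver the stated 80% power: the printed inputs need about 264, and 207 with 20% drop-out gives about 71%

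*Protocol article*

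**What the plan says.** The Sample size section of the protocol article gives two calculations. The first, for health-related quality of life (the primary outcome), gives 107 women per group. The second is for regular leisure time physical activity, which the authors regard as the outcome hardest to achieve. Its inputs are all printed:

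- Baseline: "It was assumed that only 17% of women in Mexico engaged in some type of regular leisure time physical activity".
- Effect: "a positive increase of at least 10% will be achieved after women participation in the IHCM".
- Method: "we used the formula to test the difference of proportions between two populations".
- Error rates: "with a = 0.05 (one side) and the power of 80" per cent.
- Result: "The total number of women by group to include assuming a drop-out rate of 20% will be 207".

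The 207 is therefore presented as an enrolment figure that already allows for drop-out. The section does not say in so many words which of 107 and 207 is the recruitment target, although 207 is the larger and the natural reading. The Statistical analysis section plans absolute percentage differences with 95% confidence intervals for this outcome.

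**The concern.** A one-sided 5% test with 80% power for 17% versus 27% needs a little over 200 evaluable women per group. The printed 207 is about that size, yet it is said to include a 20% drop-out allowance. Both cannot be true under the printed inputs.

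What is at stake is how a null result would be read. This is the outcome that sets the larger sample size. A reader who sees no significant difference in physical activity would take it as coming from a comparison with a 20% chance of missing a 10-point gain. If the assumed drop-out occurs, that chance is about 29%.

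**Working it through.** **Inputs** (all from Sample size): p1 = 0.17; p2 = 0.27, reading the 10% increase as percentage points; one-sided alpha 0.05, so z = 1.645; power 80%, so z = 0.8416; drop-out 20%; equal groups.

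**Step 1: evaluable women needed per group.** With p̄ = (0.17 + 0.27)/2 = 0.22, the pooled formula is

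n = [1.645·√(2·p̄(1−p̄)) + 0.8416·√(p1(1−p1) + p2(1−p2))]² / (p2−p1)²

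- √(2 × 0.22 × 0.78) = 0.5858, and × 1.645 = 0.9637
- √(0.17 × 0.83 + 0.27 × 0.73) = √0.3382 = 0.5815, and × 0.8416 = 0.4894
- n = (0.9637 + 0.4894)² / 0.01 = 211.1

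**Step 2: add drop-out.** 211.1 / 0.8 = 263.9, about 264 per group (265 if n is first rounded up to 212).

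**Step 3: try to reproduce 207 with other common versions.** One-sided 0.05, 80% power, 17% versus 27%:

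| Version | Evaluable n | n / 0.8 | n × 1.2 |
|---|---|---|---|
| Pooled variance | 211.1 | 263.9 | 253.4 |
| Unpooled variance | 209.1 | 261.4 | 250.9 |
| Arcsine | 209.7 | 262.1 | 251.7 |
| Continuity-corrected | 230.7 | 288.4 | 276.8 |

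No inflated figure is near 207; only the uninflated ones are. A two-sided test moves further away, to 332 to 335 after drop-out (360 with continuity correction). Reading 10% as a relative increase (17% to 18.7%) gives about 7,840 per group.

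One calculation does return 207: 17% versus 7%, two-sided 0.05, pooled, needs 165 evaluable, and 165 / 0.8 = 206.25, rounded up to 207. It uses a fall of 10 points (or a 7% baseline) and a two-sided test, and so contradicts the printed increase from 17% and the printed one-sided test.

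**Step 4: power that 207 gives.** Evaluable women: 207 × 0.8 = 165.6, about 166 per group.

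Power = Φ{[(p2−p1)·√n − z·0.5858] / 0.5815}

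- One-sided, n = 165.6: [0.10 × 12.869 − 1.645 × 0.5858] / 0.5815 = (1.2869 − 0.9637) / 0.5815 = 0.556, so power is 71%.
- Two-sided 0.05 (z = 1.960): (1.2869 − 1.1482) / 0.5815 = 0.239, so power is 59%.
- With no drop-out (n = 207), one-sided: 79.3%.

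**Step 5: difference detectable with 80% power at 165.6 per group.** Solving the same formula for p2 from p1 = 0.17 gives 28.4% one-sided (11.4 points) and 30.0% two-sided (13.0 points).

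**The case against.** The arithmetic is not in dispute; the case on the other side concerns its weight and its remedy.

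- **Secondary outcome.** Physical activity is listed among the other outcome variables, and 207 is nearly double the 107 given for the primary outcome. This stands: the primary sample size is not threatened. But the authors chose to size the study for this outcome and attached an explicit power claim to it, and that claim is wrong.
- **The 71% is conditional.** It applies only if the full 20% is lost; with all 207 evaluable, power is 79.3%. This is correct, and the condition must be stated. It does not rescue the text, which says that 207 already allows for 20% drop-out.
- **The origin of 207 is unknown.** The allowance may have been left out, or a different calculation may have been run (17% versus 7%, two-sided), in which case the allowance is in the figure and the printed inputs are wrong. The document cannot settle this. Either way, the printed inputs and the printed result do not agree, and 166 evaluable women give 71% power for 17% versus 27%.
- **The 71% is not the power of the full planned analysis.** It assumes two independent samples compared once, whereas the plan has repeated measurements, difference-in-differences and one clinic per group. This also stands. The restated figure should be labelled as the result of the stated two-proportion formula, which is the basis the authors chose.
- **Two-sided figures are a side issue.** The text states a one-sided test. They are given only because the planned 95% intervals correspond to a two-sided 0.05 test; the finding does not depend on them.
- **Which size governs is a small point.** 207 is the natural reading, and one clause settles it.

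**Conclusion.** Wrong as written. Under the inputs in the Sample size section, 80% power needs 209 to 211 evaluable women per group and about 261 to 264 enrolled. The stated 207 is short by about 54 to 57 per group, roughly a fifth, and lies below the requirement even without drop-out. After the stated 20% loss it gives 71% power one-sided (59% two-sided) for a 10-point increase.

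This rests on reading 10% as percentage points, on equal groups, on the stated formula for two independent proportions without continuity correction, and on the full 20% being lost. A continuity correction or a relative reading of the increase would widen the gap. Clustering by clinic is not included in these figures.

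**What to change.** In the Sample size section:

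1. State that 207 per group is the enrolment target, if that is the intention, so that it is not left beside 107 without explanation.
2. Delete the claim of 80% power for a 10-point difference and replace it with wording such as: *By the two-proportion formula, 207 women per group with 20% drop-out (about 166 evaluable) give 71% power at one-sided 0.05 (59% at two-sided 0.05) for 17% versus 27%, and 80% power for 17% versus about 28.4% (one-sided) or 30% (two-sided).*
3. Check the original calculation. If a printed input (baseline, direction of change or sidedness) is the error, correct it and recompute the power from the corrected inputs.

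The cost is wording only. The stated power becomes less favourable, and neither the design nor the number of women changes. Keeping the 80% claim for 10 points would instead mean enrolling about 264 per group, 57 more in each.

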### Statistical analysis

The women characteristics of each intervention and comparison groups will be compared by using the Chi-square test to ascertain whether the groups were equivalent.

The effects of intervention for categorical outcome variables (regular leisure time physical activity, healthy diet) will be measured by comparing the baseline and post-intervention evaluation stages for differences in these variables using Chi-square test. Absolute percentage differences and corresponding 95% confidence intervals will be calculated.

Scores for the HR-QoL on the WHQ23 scale, the self-efficacy on the PHS-ES scale, the empowerment on the short form scale, knowledge about the climacteric stage, and menopause and self-care-related activities will be calculated according to the scoring algorithms. Measures of central tendency and distribution will be examined for these variables at the different measurement periods. The differences in the baseline and post-intervention stages for outcome variables will be compared within each group, and differences between the groups will be compared using the differences-in-differences (D-in-D) estimator [52]. The generalized linear model (GLM) will be used to assess changes in the main outcome variable controlling for baseline measures and other study variables as covariates. The GLM methods allow for modeling the correlation of the repeated observations on the same subjects [53].

The p value <0.05 will be considered as statistically significant. The analysis will be performed with the Stata 11.0 statistical software (Stata 11.0, Stata Corp; College Station, TX).

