5) Percentage of women who practice regular leisure time physical activity (PA), where regular was defined as moderate intensity if done for ≥150 minutes/week or vigorous intensity if done ≥75 minutes/week.

6) Percentage of women who practice a healthy diet, which included the daily consumption of fruits (3-4 servings), vegetables (4-5 servings), and dairy products (2-3 servings).

The covariates will be:

a) Women's general characteristics: Age, schooling, marital and employment status.

b) Smoking status and alcohol consumption. Smoking status will consider former and current smokers and will register the number of cigarettes actually smoked per day. Alcohol consumption will be classified as non-drinkers (never drink alcohol), occasional drinkers (drink rarely or less than once a week), moderate drinkers (from 1 to 14 drinks per week) and heavy drinkers (more than 14 drinks per week).

c) Nutritional status will be measured by body mass index (BMI) and classified into groups of normal weight (BMI of 18.5-24.9 kg/m^2^), overweight (BMI of 25.0 to 29.9 kg/m^2^), or obese (BMI ≥30.0 kg/m^2^).

d) Social support (SS) will be measured by applying the DUKE-UNC-11 questionnaire [46]. This questionnaire evaluates confidential SS (possibility of having people to communicate with) with a minimum score of 7 points (low confidential SS) and a maximum score of 35 points (high confidential SS); and affective SS (demonstration of love, affection, and empathy) with a minimum score of 4 (low affective SS) and a maximum score of 20 points (high affective SS).

e) Medical and reproductive history: Presence of chronic diseases, number of pregnancies and living children, and menopause (one year after the last menstrual period). Type of menopause will be classified as natural or surgical, age at onset of menopause; time elapsed since menopause, presence and type of climacteric symptoms, and number of visits with the family doctor or other health provider in the last three months. The severity of vasomotor symptoms and vaginal atrophy symptoms is classified using the criteria proposed by the Department of Health and Human Services Food and Drug Administration [47], which are based upon women's self-report, and define the symptoms as mild, moderate, or severe.

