## Discussion

In primary care services, it is essential to provide a source of care that has continuity and coordination, and comprehensively covers the health needs of people. The constraints resulting from limited resources and restrictive organizational characteristics of institutionalized healthcare allows a limited range of changes, and these circumstances promote that innovative healthcare models should be carefully designed and evaluated to demonstrate healthcare service relevance and feasibility. Relevance, in this case, refers to meeting the health needs of climacteric stage women and to demonstrating its potential benefit. Feasibility means that the new model of care is applicable in the local context. An integrative health care model (bio-psycho-social, multidisciplinary and women-centered) with the empowerment approach may be a better alternative to ensure that women engage in their self-care and understand its importance to their present and future health and quality of life. The evaluation of the effectiveness of this research-based model can guide the feasibility of extending it into an operational model through a specific program.

The possible limitations of the study may include the following:

It was decided to perform the intervention in one clinic, taking another as a control to prevent women from both groups from communicating and transmitting information between them. However, the implementation of the study in two clinics may result in difference baseline characteristics of women in both groups. To overcome this limitation in the data analysis step, the regression methods will be used to adjust the results of the study for possible differences between groups.

Furthermore, the baseline evaluation can affect women in the control group resulting in them seeking counseling regarding the climacteric stage, attending screening programs, and changing their lifestyles.

The request for voluntary collaboration of family doctors and women could result in better doctors and women with healthier lifestyles agreeing to participate. Previous studies have reported that patients with unhealthy lifestyles are usually reluctant to participate. To confirm or disregard this limitation we will apply a short list of questions about the general characteristics and lifestyles to women who do not agree to participate in the study.

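### A non-significant chi-square test cannot show that the two clinics' women are equivalent, and the analysis section names no covariate adjustment for physical activity and diet

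*Protocol article*

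**What the plan says.** The Methods/Design section describes one intervention clinic and one comparison clinic, both chosen for convenience. Women are not randomised.

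The Statistical analysis section says that the characteristics of the two groups "will be compared by using the Chi-square test to ascertain whether the groups were equivalent". The only criterion given is "The p value <0.05 will be considered as statistically significant". No margin is stated within which groups would count as equivalent.

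On the outcomes, the same section plans:
- for the score outcomes, comparisons of change within each group and a difference-in-differences estimate between groups;
- for the main outcome (HR-QoL), a generalized linear model that controls for baseline measures and other study variables;
- for regular leisure-time physical activity and healthy diet, chi-square tests of baseline against post-intervention stages, with absolute percentage differences and 95% confidence intervals. No adjusted model is named for these two.

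The Discussion accepts that using two clinics may leave the groups different at baseline and says that "regression methods will be used to adjust the results of the study for possible differences between groups". The covariates are listed under Study variables, beginning with "Women's general characteristics: Age, schooling, marital and employment status".

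**The concern.** With one convenience clinic per arm, comparability of the women is a main condition for reading a difference as an effect of the care model. The plan gives the task of confirming it to a test that cannot do so. A non-significant chi-square result is expected both when groups are alike and when they differ by an amount too small for the sample to detect.

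At stake is how the results are read. A baseline table that declares the clinics equivalent lends weight to any outcome comparison made without adjustment. In the analysis section, physical activity and diet are the outcomes for which only unadjusted comparisons are named. The section and the Discussion therefore leave open whether these two outcomes will be adjusted at all.

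**Working it through.** **Inputs from the Sample size and Statistical analysis sections**
- Women per group: 107 for HR-QoL ("The number of women by group, assuming a drop-out rate of 20% will be 107") and 207 for physical activity ("The total number of women by group to include assuming a drop-out rate of 20% will be 207"). Baseline is measured at entry, so the full recruited numbers are used, which favours the plan.
- Significance level 0.05, taken as two-sided for a chi-square test.
- Physical activity: 17% at the outset with a 10% increase, read as 17% to 27%.

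**Assumed, because the document gives no figure:** true imbalances of 5, 10 and 15 percentage points, at prevalences of 17%, 30% and 50%.

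**The plan's own figures.** No figure is stated for the equivalence check. The two group sizes serve only as inputs, but I tried to reproduce them.
- HR-QoL uses "a mean HR-QoL score of 64.9 points (standard deviation of 23.4 points) in the domain of general well-being", a 10-point difference and "α = 0.05 (for one-sided hypothesis) and β = 0.20". One-sided: 2 × (1.645 + 0.842)² × (23.4/10)² = 67.7, and 67.7/0.8 = 84.6, so 85. Two-sided: 2 × (1.960 + 0.842)² × (23.4/10)² = 86.0, and 86.0/0.8 = 107.4. The stated 107 fits the two-sided form.
- Physical activity, 17% v 27%, one-sided: 212 per group before drop-out and 265 after. The stated 207 is not reproduced as a number that includes drop-out.

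These mismatches are separate matters. The point here does not depend on them.

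**Chance that the test is non-significant despite a true imbalance.** With n per group, p̄ = (p1 + p2)/2, SE0 = √(2p̄(1 − p̄)/n) and SE1 = √((p1(1 − p1) + p2(1 − p2))/n):

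power = Φ((|p2 − p1| − 1.96 × SE0)/SE1); miss = 1 − power.

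Example, 17% v 27% at n = 107: SE0 = 0.0566, SE1 = 0.0562, (0.10 − 1.96 × 0.0566)/0.0562 = −0.20, power 42%, miss 58%.
Example, 50% v 60% at n = 207: SE0 = 0.0489, SE1 = 0.0487, (0.10 − 1.96 × 0.0489)/0.0487 = 0.085, power 53%, miss 47%.

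| True imbalance | Missed at 107 | Missed at 207 |
|---|---|---|
| 17% v 22% | 85% | 75% |
| 30% v 35% | 88% | 81% |
| 50% v 55% | 89% | 83% |
| 17% v 27% | 58% | 31% |
| 30% v 40% | 67% | 43% |
| 50% v 60% | 69% | 47% |
| 50% v 65% | 40% | 13% |

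The 17% v 27% row equals the whole gain on which the physical activity sample size is built.

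**What showing equivalence would take.** Two one-sided tests at 0.05 with 80% power, no true difference and an assumed margin of ±10 points need n = 2p(1 − p) × ((1.645 + 1.282)/0.10)² analysed women per group. This gives 242 at 17%, 360 at 30% and 429 at 50%. Both planned sizes are smaller.

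**Which outcomes depend on the baseline check**
- HR-QoL: difference-in-differences removes constant level differences, and the generalized linear model adjusts for measured covariates. Neither is conditional on the chi-square result.
- Self-efficacy, empowerment and knowledge: difference-in-differences, with no covariates named.
- Physical activity and diet: chi-square tests and percentage differences in the analysis section; covered only by the Discussion's general statement on regression.

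**The case against.** The strongest reply is that the protocol expects the clinics to differ and plans for it. The Discussion's promise covers the results of the study in general, the main outcome has an adjusted model, and no text makes adjustment depend on a baseline p-value. This stands. A reader might infer that a missed imbalance would shift the HR-QoL effect by some number of points. The document does not support that: such a shift belongs to an unadjusted comparison of HR-QoL levels, which is not planned.

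A reader might also infer that the baseline test is all that guards the activity and diet results against confounding. That goes too far, because the Discussion's statement can be read to cover them, and the difference-in-differences sentence refers to outcome variables without a clear limit.

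A third reply is that the activity and diet chi-square compares stages over time, and baseline differences between clinics do not confound a change within one group. That is correct on that reading. But a change within one group does not isolate the effect of the care model, and the section then names no adjusted comparison between groups for these outcomes.

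Fourth, how often imbalances are missed depends on their size, which is assumed. Large ones would usually be flagged, as the 15-point row shows at 207 per group. This limits the claim to small and moderate imbalances. It does not turn a test of difference into a test of equivalence.

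Finally, naming only chi-square when some covariates are scores is baseline-table detail that an article may condense. I do not press it as a separate fault.

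**Conclusion.** The concern holds in a limited form. The stated purpose of the chi-square test is one it cannot serve. At the planned sizes a true 10-point imbalance would be missed about 58-69% of the time at 107 per group and 31-47% at 207. These rates rest on assumed imbalances and prevalences and on a two-sided 0.05 test.

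The consequence for HR-QoL is small as far as measured covariates go. The practical gap is in physical activity and healthy diet, where the analysis section and the Discussion do not agree on whether adjustment will be made, and to a lesser degree in the other secondary scores, for which no covariates are named. No bias in points or percentages can be put on this from the document. The change is worth making because it is nearly free and reduces exposure to bias in a non-randomised comparison.

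**What to change.** 1. Delete the statement that the test ascertains equivalence.
2. Describe baseline balance with standardised differences, or differences with 95% confidence intervals, for each covariate on its original scale. Use them as description and not as a pass/fail rule. A cut-off of 0.1, for example, would be crossed by chance alone for about 31% of covariates at 207 per group (SE = √(2/207) = 0.098) and 46% at 107 (SE = √(2/107) = 0.137).
3. Carry the Discussion's promise into the Statistical analysis section. Compare activity and diet between groups with a logistic or other generalized linear model adjusted for the baseline value of the outcome and the listed baseline covariates. Adherence is listed with the covariates but arises after entry, so it does not belong in that set.
4. Apply the same covariates to the other secondary outcomes, regardless of any baseline p-value.

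The cost is some rewording, a changed column in the baseline table and a few more models. All data needed are already to be collected, and the design and recruitment are unaffected.
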